#### Measures of adherence

Our primary measure of adherence will be data obtained from medication monitoring boxes.^27^ The boxes will not be set up act as a reminder system. Other measures will also be used and compared with this. These will include pill counts (the remaining medication in the box at the end of each month) and also patient-reported adherence, where we will ask patients to estimate how many doses they have missed in the last month. In the case of DOT or VOT methods being used, a record of missed doses will be kept.

#### Administration of the manualised intervention

The patient’s case manager (usually the TB clinic nurse), plus a study research nurse, will apply the intervention in partnership with the patient to identify whether personal, sociocultural and/or systems risk factors are present that suggest likely poor adherence with treatment. If these are identified, then the relevant measures outlined in the manualised intervention that may mitigate these will be reviewed and implemented with the agreement of the participant. These will be continued throughout the course of treatment or stopped if no longer deemed to be relevant or required on reassessment.

#### Study schedule of visits

Study subjects will be seen at weeks 0, 2, 4, 8, 12, 16, 20 and 24 (earliest date of treatment completion). Should they require ongoing treatment after 6 months, they will be seen as clinically indicated. At each review, adherence assessments will be performed, in addition to an assessment of PAPA, the completion of the BMQ and the EQ-5D-5L Quality of Life questionnaires^23 28^ and the GAD-7^29^ and PHQ-9^30^ to assess anxiety and depression. The manualised intervention will be applied if the patient is attending a clinic that has been randomised to the intervention arm. All data will be collected by the research nurse using standardised forms.

#### Follow-up

Most patients who do not have clinically important drug-resistant disease receive 6 months of treatment. To allow for treatment interruptions, patients within the pilot study will be followed up to either treatment completion or for a total of 9 months from starting anti-TB therapy.

#### Analysis and interpretation

Where possible, univariable analyses will be undertaken to compare each outcome measure listed between study arms (intervention and control). For the primary outcome (adherence), the mean percentage value will be reported by arm (intervention and control) and histograms will be used to describe the distribution of values by study arm. Binary secondary outcomes will be reported by the proportion of individuals achieving the outcome within each arm. The need to adjust for clustering by site and clinical care provider will be assessed using the cluster summary method (a t-test) to compare the cluster means or proportions (as appropriate, between arms). An assessment of the balance in baseline characteristics between the study arms will also be conducted. If randomisation has failed to evenly distribute key characteristics (eg, age, sex, ethnicity or other factors identified as important during the scoping reviews), then the cluster means or proportions will be adjusted for these differences before applying the t-test. This two-stage approach to analysis is described by Hayes and Moulton.^31^ We recognise that adherence data may be highly skewed and thus may require compensatory analytical approaches.

The analysis of the first three of our secondary outcomes will address the feasibility of a definitive trial following a similar design to the pilot. Analysis of secondary outcomes 4–6 addresses the intervention, and complements the process evaluation (see below). Analysis of the primary outcome and final secondary outcomes around treatment adherence and completion provides initial information—given the modest sample size—concerning the effectiveness of the intervention, and may assist the sample size calculation for the definitive trial. They can also offer an alert in the unlikely event that the intervention is harmful.

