#### Outcomes of the pilot

The primary outcome of the study will be level of adherence, measured as the proportion of prescribed doses taken and assessed at 6 months from the start of treatment. In addition to this primary outcome, a number of secondary outcomes will also be measured, as follows:

Proportion consenting to the study.Completeness of data for measures of adherence.Proportion of patients withdrawing during the study and the reasons why.Proportion of patients identified as needing adherence support in the intervention arm.Proportion of patients offered adherence support and accepting it in the intervention arm.Documentation of which adherence-promoting activities have been implemented among patients both in the standard of care and intervention arm, and when.Detailed treatment implementation information: for example, proportion of patients completing treatment, proportion of patients still on treatment after 9 months or at study completion (whichever is the earlier).Patterns of adherence (implementation and discontinuation).Impact of manualised intervention on maintaining adherence over the duration of treatment.Process variables: adherence-related PAPA.

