#### Process measures, recruitment and eligibility

Process measures for each element of the package will be developed once the manual development has been completed and will be used to assess success. They will include acceptability, uptake and change in practice. We will work with patients and staff separately at all four London sites. We will interview 20 patients (5 at each study site, ie, 10 from each arm) and, if possible, 20 healthcare workers (5 at each site). The patients will be selected within each site using purposeful sampling of clinic lists of every patient with active TB, to enable us to reflect the demographic spread of patients.

Key outputs will include a qualitative evaluation of delivery, the development of a narrative description of the process of intervention implementation and maintenance, and a quantitative assessment of adherence-related PAPA within intervention and control groups.

We will invite participation in the process evaluation from patients enrolled in the pilot study or staff members treating patients at one of the four London sites also involved in delivering the pilot study. They will be included if they are aged 18 years or over and able to provide informed consent. This will include probing anticipated versus real-life delivery of the intervention.

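### The perceptions-and-practicalities outcome has a week-0 score that the planned arm comparison does not commit to using, so precision and protection against chance imbalance between four clinics may be lost (low severity)

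*Protocol article*

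**What the plan says.** All references are to the protocol article.

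- **Outcome.** The last item in the secondary outcome list (Outcomes of the pilot) is "Process variables: adherence-related PAPA". Under Process measures, recruitment and eligibility, the key outputs include "a quantitative assessment of adherence-related PAPA within intervention and control groups".
- **Measurement.** Study schedule of visits: "Study subjects will be seen at weeks 0, 2, 4, 8, 12, 16, 20 and 24", and "At each review, adherence assessments will be performed, in addition to an assessment of PAPA, the completion of the BMQ". A week-0 value of this outcome is therefore collected.
- **Default analysis.** Analysis and interpretation: "Where possible, univariable analyses will be undertaken to compare each outcome measure listed between study arms (intervention and control".
- **Adjustment.** The same section adds: "An assessment of the balance in baseline characteristics between the study arms will also be conducted". The trigger is "If randomisation has failed to evenly distribute key characteristics (eg, age, sex, ethnicity or other factors identified as important during the scoping reviews"; in that case, "then the cluster means or proportions will be adjusted for these differences before applying the t-test". This is the two-stage cluster-summary method.
- **Design.** Four clinics are randomised, two per arm, with a target of 20 patients each. The section on study design, recruitment and eligibility says that formal hypothesis testing is not the pilot's purpose.

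**The concern.** The primary outcome, the proportion of doses taken, has no baseline, because patients already on treatment are excluded. PAPA/BMQ does have one, and a patient's own earlier score is usually among the strongest predictors of a later score on the same scale. The plan gives an analysis for every listed outcome but does not commit to using this score. The score could come in only through a rule that depends on observed imbalance, states no threshold, and gives age, sex and ethnicity as its named examples.

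Two things are at stake. First, with only four randomised units, the arms may well differ on beliefs before anyone is treated, and part of that difference would persist into an unadjusted follow-up comparison. Second, adjusting only when imbalance is seen does not secure the gain in precision that routine adjustment can bring. PAPA shows whether the manual shifts the beliefs and practical barriers it targets, and the process evaluation feeds the final package for a definitive trial.

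**Working it through.** **The plan's own figures.** The article gives no power or precision for PAPA/BMQ. Table 1 concerns adherence only. Its nine powers are reproduced to within 0.01 by a two-sided 5% comparison of two proportions with 40 independent patients per arm, but they have no bearing on this point.

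**Inputs from the article.** 2 clinics per arm; 20 patients per clinic; a t-test on cluster summaries, so 4 − 2 = 2 df, critical t 4.303 (two-sided 5%, assumed).

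**Assumed inputs (not in the article).** ICC 0.01, 0.05 or 0.10; correlation of week-0 with follow-up score ρ = 0.3, 0.5 or 0.7; equal variance at both times; results in outcome SDs.

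**Step 1: chance week-0 difference between arms.** The variance of a clinic mean is v = ICC + (1 − ICC)/20. The SD of the difference between two arms of two clinics is √(2v/2) = √v.

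| ICC | v | SD of difference | P(absolute difference > 0.25 SD) |
|---|---|---|---|
| 0.01 | 0.01 + 0.0495 = 0.0595 | 0.24 | 31% |
| 0.05 | 0.05 + 0.0475 = 0.0975 | 0.31 | 42% |
| 0.10 | 0.10 + 0.0450 = 0.1450 | 0.38 | 51% |

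**Step 2: the part carried forward.** Given a week-0 difference D, the expected shift in an unadjusted follow-up contrast is about ρ × D. For D = 0.25 this is 0.075, 0.125 or 0.175 SD at ρ = 0.3, 0.5 or 0.7. Only a part carries over, and over all randomisations it averages to zero.

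**Step 3: precision with week-0 adjustment.** If ρ is the same within and between clinics, the variance is multiplied by 1 − ρ², that is 0.91, 0.75 or 0.51, and the SE by 0.95, 0.87 or 0.71. At ICC 0.05 and ρ = 0.5:

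- Unadjusted: SE = √0.0975 = 0.312; 95% CI half-width 4.303 × 0.312 = 1.34 SD.
- Adjusted: SE = √(0.75 × 0.0975) = √0.0731 = 0.270; half-width 4.303 × 0.270 = 1.16 SD.
- Power (noncentral t, 2 df): 31% to 38% for a 0.8 SD effect, 16% to 20% for 0.5 SD.

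A simulation of 5,000 trials per setting agreed: empirical SE 0.31 against 0.27, with type I error between 4.5% and 5.3% for both methods.

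**Step 4: the unfavourable case.** Keep ICC 0.05 and a slope of 0.5, but let clinic-level week-0 and follow-up means be uncorrelated. The clinic part becomes 0.05 × (1 + 0.5²) = 0.0625 and the patient part 0.0475 × 0.75 = 0.0356. The total is 0.098 against 0.0975 unadjusted, so there is no gain.

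**Step 5: level of adjustment.** A clinic-level covariate would leave 1 df, with critical t 12.71. At ρ = 0.5 the half-width would change by 0.866 × 12.71/4.303 = 2.6 times. Adjustment must therefore be made on individual scores in stage 1.

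**The case against.** - **The contrast is valid as planned.** A reader might infer that clinic differences present before treatment will be read as an intervention effect. The documents do not support that. Clinics are randomised, and the cluster-level t-test counts between-clinic variation as error; type I error was held without adjustment. This objection stands, and it confines the point to precision and chance imbalance.
- **The plan has an adjustment rule.** Its list is open-ended. The scoping reviews cover personal, social and cultural factors, and the Introduction names perceptions and beliefs among barriers to adherence, so week-0 beliefs could qualify. This stands in part. The score is not named, and a rule triggered by observed imbalance does not secure the precision gain.
- **A follow-up-only comparison is not stated.** Comparing change scores is also univariable, and the article does not say how the repeated scores are summarised. This stands: the plan does not exclude use of week 0, but it does not commit to it.
- **The gain is small and rests on assumptions.** An interval of ±1.16 SD is hardly more informative than ±1.34 SD, and the gain vanishes without clinic-level correlation. This stands and keeps the severity low.
- **Covariates for a secondary score belong in the full protocol or analysis plan.** This is a fair point. However, the article does fix a default analysis for every listed outcome, and a better one is available from data already collected. The order of questionnaires and manual at week 0, taken alone, is only unstated detail and no error.

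**Conclusion.** The point holds in a limited form. PAPA/BMQ is measured at week 0. The stated default is a univariable comparison, and adjustment depends on observed imbalance in a list that does not name the outcome's own baseline. Always using that baseline would be the better method and costs no data.

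The sizes depend on an ICC and correlations that the article does not give. A week-0 difference above 0.25 SD has a chance of about 31% to 51% for ICC 0.01 to 0.10. The SE reduction is about 13% at ρ = 0.5 at both levels, and nil if clinic means at the two times are unrelated. Nothing here shows bias or an invalid test, and the primary outcome is unaffected. For a secondary process variable in a pilot not meant for formal testing, severity is low.

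**What to change.** In Analysis and interpretation, state that for PAPA/BMQ:

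- the patient's own week-0 score is always a covariate, whether or not imbalance is seen;
- it enters stage 1 of the two-stage method at individual level, in a model for the follow-up score without study arm;
- stage 2 applies the t-test to the four clinic mean residuals, keeping 2 df, with no cluster-level covariate.

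In Study schedule of visits, state that the week-0 score used as baseline is taken before the manual is first applied, so that it is a pre-intervention value in both arms.

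The cost is about one sentence in each section, with no new data, staff or patients. The small downside is that patients without a week-0 score need a simple stated rule, for example mean imputation of the baseline.

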### Piloting the intervention

#### Study design, recruitment and eligibility

Once the intervention is developed, proof of concept is required within the real world. This will be undertaken using a non-blinded cluster randomised pilot study that compares the manualised intervention to the usual standard of care in four London clinics treating TB. Two clinics will be randomly allocated to the intervention and two to standard of care. In the latter, the amount of support provided to patients is based on perceived need, as identified by a nurse-led review and a needs assessment. Most patients will have supported self-administered therapy, while others will be offered DOT and/or VOT if this is felt to be appropriate. We anticipate enrolment to commence in January 2020.

All consecutive patients aged 18 or over who are about to start treatment for TB, irrespective of the site of disease, will be approached to take part in the study. We will exclude individuals who are unable to provide informed consent, those already on treatment and those who are not expected to live for the duration of the study (a minimum of 6 months from starting treatment). Within the pilot study, it is essential to capture the entire treatment period for each patient in order to assess the effectiveness of the intervention. Due to the nature of the TB patient population in the UK, patients are likely to include people at greater risk of poor adherence, such as migrants newly arrived in the UK, people whose first language is not English, people with a mental health disorder, people taking immunosuppressive therapy or known to have immunodeficiency, those with a previous history of treatment for TB, or poor adherence with anti-TB medication, and people with a current or previous history of drug or alcohol misuse.

The purpose of the pilot study was not formal hypothesis testing. Given this, a target sample size of 80 patients enrolled (20 per site) was identified for the pilot study as providing useful information that can help determine whether the intervention will be deliverable within a clinical setting. It will also guide the development of a possible larger definitive study using the intervention. The four TB clinics of interest (in East and North London) each treat in excess of 60 relevant patients per annum.

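### Clinics are randomised, yet adjustment for clustering depends on an assessment of need, and the test named for that assessment cannot show whether it is needed

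*Protocol article*

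**What the plan says.** The protocol article, under Study design, recruitment and eligibility (pilot), describes a "non-blinded cluster randomised pilot study that compares the manualised intervention to the usual standard of care in four London clinics treating TB". The allocation is by clinic: "Two clinics will be randomly allocated to the intervention and two to standard of care". The size is "a target sample size of 80 patients enrolled (20 per site) was identified for the pilot study".

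Under Outcomes of the pilot, the primary outcome is a per-patient percentage: "The primary outcome of the study will be level of adherence, measured as the proportion of prescribed doses taken and assessed at 6 months".

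Analysis and interpretation then proceeds in this order:

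- It opens with "Where possible, univariable analyses will be undertaken to compare each outcome measure listed between study arms (intervention and control").
- It describes adherence by arm (mean and histograms) and binary outcomes by arm (proportions).
- It states: "The need to adjust for clustering by site and clinical care provider will be assessed using the cluster summary method (a t-test"), the t-test being a comparison of cluster means or proportions between arms.
- It adds that, if baseline characteristics are unbalanced, the cluster summaries will be adjusted before the t-test is applied, and calls this a two-stage approach.

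The Power calculation section gives Table 1 as the power of the primary analysis for 80 individuals, 40 per arm. No ICC or design effect is given anywhere.

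**The concern.** There are two faults in the sentence on clustering.

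1. **It makes adjustment conditional.** When clinics are the randomised unit, patients within a clinic share an allocation, so between-arm inference has to reflect between-clinic variation whether or not the data seem to show any.
2. **The named check does not answer the question asked.** A t-test of cluster means between arms tests the intervention effect. Between-clinic variation enters only its denominator. A non-significant result says nothing about whether clustering can be ignored, and with no intervention effect a valid 5% test is non-significant 95% of the time. An analyst who read non-significance as no need to adjust would nearly always fall back on treating patients as independent.

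At stake is how far the between-arm results can be trusted. The protocol plans to use them as initial information on effectiveness, as help with the sample size of the definitive trial, and as an alert to harm. A patient-level comparison could present a chance difference between two pairs of clinics as an intervention effect, with too narrow an interval.

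**Working it through.** **Inputs from the protocol.** Four clinics, two per arm, 20 patients per clinic, 40 per arm.

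**Assumptions.** Two-sided 5% level (not stated, but it reproduces Table 1); ICC from 0.01 to 0.10; equal clinic sizes; normal outcomes for the error rates. Clustering by provider within clinic is not modelled.

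**1. Reproduce Table 1.** For two independent proportions with pooled variance under the null and n = 40 per arm:

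power = Φ{ [ |p2 − p1|√n − 1.96√(2p̄(1 − p̄)) ] / √[ p1(1 − p1) + p2(1 − p2) ] }

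For the 80 + 20 row: (0.2 × 6.325 − 1.96 × √0.18) / √0.16 = (1.265 − 0.832) / 0.4 = 1.083, so power is 0.861 (stated 0.86). All nine rows:

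| Baseline + increase | Stated | Recomputed |
|---|---|---|
| 70 + 30 | 0.98 | 0.976 |
| 60 + 30 | 0.88 | 0.888 |
| 50 + 30 | 0.82 | 0.816 |
| 80 + 20 | 0.86 | 0.861 |
| 70 + 20 | 0.61 | 0.612 |
| 60 + 20 | 0.49 | 0.497 |
| 90 + 10 | 0.54 | 0.538 |
| 80 + 10 | 0.24 | 0.237 |
| 70 + 10 | 0.18 | 0.175 |

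Every row agrees within one percentage point with a design effect of 1. Unpooled, continuity-corrected, arcsine, exact chi-square and Fisher versions each failed on at least one row. Table 1 is thus a calculation for 40 against 40 independent patients.

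**2. What the named t-test responds to.** With two clinics per arm, T = (difference between the arms' averages of clinic means) / √s², where s² is the pooled within-arm variance of clinic means, on 2 df. In simulation with no intervention effect (100,000 replicates per ICC), it rejected 4.9% to 5.1% of the time at every ICC from 0 to 0.20. It is a valid test of the intervention, and for that reason its result under the null does not depend on how much clustering there is.

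**3. Error rate if patients are compared as independent.** The design effect is 1 + 19 × ICC. The approximate error rate is 2[1 − Φ(1.96/√design effect)]. At ICC 0.05, for example, 1.96/√1.95 = 1.404, giving 16.0%.

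| ICC | Design effect | Patient-level, formula | Patient-level, simulated | Cluster t-test, simulated |
|---|---|---|---|---|
| 0.01 | 1.19 | 7.2% | 7.2% | 4.9% |
| 0.05 | 1.95 | 16.0% | 16.4% | 4.9% |
| 0.10 | 2.90 | 25.0% | 25.7% | 4.9% |

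**4. Interval width.** The patient-level interval omits the design effect and uses a multiplier of 1.99 (78 df) instead of 4.30 (2 df). The appropriate interval is wider by about (4.30/1.99) × √design effect:

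- ICC 0.01: 2.16 × 1.091 = 2.4
- ICC 0.05: 2.16 × 1.396 = 3.0
- ICC 0.10: 2.16 × 1.703 = 3.7

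**5. What the cluster-level analysis does to Table 1.** Keep Table 1's binary variance. The non-centrality is (p2 − p1) / √{ [p1(1 − p1) + p2(1 − p2)]/40 × design effect }, referred to a t-distribution on 2 df.

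| Row | Stated | ICC 0 | ICC 0.01 | ICC 0.05 | ICC 0.10 |
|---|---|---|---|---|---|
| 80 + 20 | 0.86 | 0.42 | 0.37 | 0.26 | 0.20 |
| 70 + 30 | 0.98 | 0.59 | 0.53 | 0.38 | 0.29 |

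Even with no clustering at all, 2 df roughly halves the stated power in these rows.

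**The case against.** The best defence is that the section, read as a whole, already describes a sound analysis. The only inferential test it names is a t-test on cluster summaries, and the later condition concerns covariate imbalance, not detected clustering. The arm-level means, histograms and proportions are descriptive, and no patient-level p-value or interval is specified. The pilot also disclaims testing: "The purpose of the pilot study was not formal hypothesis testing". No go/no-go rule rests on a p-value.

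Much of this stands. It means that three stronger readings, which a reader might infer, are not supported:

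- **That the plan as written inflates the error rate two- to five-fold.** That range needs a patient-level test and an ICC of about 0.02 to 0.10. At 0.01 the factor is 1.4. The protocol gives no ICC and does not commit to a patient-level test.
- **That a preliminary significance test for a clinic effect decides the analysis.** No such test appears. The test named is the between-arm one.
- **That care providers would be used as independent units.** Provider is mentioned as a source of clustering, not as the unit of the t-test.

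What the defence does not remove is the sentence itself. It presents the cluster method as a way of assessing need and nowhere says that the method applies regardless. Table 1, described as the power of the primary analysis, rests on independent patients. The disclaimer about testing also does not protect the intervals, or the effectiveness and harm signals that the section intends to draw from the comparison.

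**Conclusion.** The point holds as a fault of wording with a realistic route to a wrong analysis. It does not show that a wrong analysis has been fixed. In a trial that randomises four clinics, adjustment for clustering is made conditional, the named assessment cannot inform that condition, and the valid two-stage method in the same section is not made unconditional.

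If the wording led to a patient-level comparison, the nominal 5% error rate would become about 7% to 25%, and the interval would be too narrow by a factor of about 2.4 to 3.7, over assumed ICCs of 0.01 to 0.10. These figures rest on equal clinics of 20 and normal outcomes. The protocol itself expects skewed adherence data, so they indicate scale only. The consequence is limited by the pilot's purpose, but the correction is cheap and should be made before analysis.

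**What to change.** In Analysis and interpretation:

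- Delete the sentence beginning "The need to adjust for clustering by site and clinical care provider will be assessed using the cluster summary method (a t-test".
- State that any between-arm inference, for outcomes measured in both arms, uses clinic-level summaries whatever clustering is observed, with 95% confidence intervals from a t-distribution on 2 df. Outcomes defined only in the intervention arm, such as needing or accepting adherence support, stay descriptive.
- State that the clinic, not the care provider, is the unit of analysis.
- Present patient-level results as description by arm.
- Report the ICC as an estimate only, not as a decision rule. With four clinics it will be imprecise.

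In Power calculation, either restate Table 1 for the cluster-level analysis over a stated range of ICCs, or label it as assuming independent patients and therefore not the power of the primary analysis.

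The cost is redrafting and one recalculated or relabelled table. Intervals will be wider and the stated power clearly lower (for the 80 + 20 row, 0.42 or less instead of 0.86). That fits a pilot that disclaims formal hypothesis testing.
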